#### Determination of sample size

Our hypothesis is that the proportion of stage 1 patients will be 50% among precarious patients versus 60% among non-precarious, a 10% absolute difference. To detect such a difference with a 90% power, 520 patients are needed (calculation made with NQUERY Advisor software). Therefore, our targeted sample size is 1040 patients (520 in each group). Inclusion period will last 36 months. Subject’s length of participation is 12 months. We recruited 20 participating sites in order to be able to include 1040 patients.

#### Statistical analysis

The strategy for design and analysis will be made in compliance with the CONSORT statement (http://www.consort-statement.org/).

Variables will be compared between the two groups according to standard tests: Student’s t test or nonparametric Wilcoxon test for quantitative parameters based on the variable distribution and chi-square test or Fisher test for proportions. The results will be presented as mean ± one standard deviation if the parameter follows a normal distribution and median [interquartile range] if the distribution is not normal for quantitative parameters. For qualitative parameters, the results will be presented as numbers (proportions).

The primary endpoint analysis will be carried out by a two-sided chi-square test on proportions. Odds ratio and its 95% confidence interval will be presented.

For secondary endpoints, the same principle will be applied for qualitative variables. For quantitative variables the mean difference and its 95% confidence interval will be presented.

All statistical analysis will be carried with SAS and R software, and the statistical significance level will be (two-sided) 0.05.

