#### Outcomes

The primary outcome is the comparison of the stage of disease at diagnosis (according to the TNM classification) between precarious and non-precarious patients.

Secondary outcomes are:
to describe the socio-economic situations and geographical context between precarious and non-precarious patients in quantitative and qualitative approaches,to describe diagnostic and therapeutic pathways of women with breast cancer including the diagnostic phase, the treatment phase and the phase of post-treatment and rehabilitation,to compare those pathways between precarious and non-precarious women,to compare in both groups of women the direct and indirect costs of care and the out-of-pocket costs.

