#### Economic analysis

The economic analysis will describe and compare the costs between the two groups of patients. The first part of analysis will reply to the question “is the precariousness in breast cancer induces over-costs from the society perspective?” This part will include the direct costs (medical direct costs (hospital and ambulatory costs) and nonmedical direct costs (transportation, home care services, social services)) and the indirect costs (productivity losses) [25, 26]. Productivity losses will be measured in terms of lost wages using human capital approach [27, 28]. The second part will reply to the question “Is the precariousness in BC induces differences in terms of out-of-pocket health expenses from patient’s perspective?” The out-of-pocket costs for treatments and follow-up, consultations with other practitioners, home help, clothing, and natural health products will be estimated, with information collected primarily from patient questionnaires before the surgery (T0) and at 3 and 6 months (T1, T2). Different types of costs are summarized in Fig. 1.

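### For skewed costs, the planned test (Wilcoxon) and summaries (medians) refer to a different quantity from the planned mean difference, and can miss or contradict it

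*Protocol article*

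**What the plan says.** All references are to the protocol article.

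- **Test (Statistical analysis).** Quantitative variables are compared by a t test or a "nonparametric Wilcoxon test for quantitative parameters based on the variable distribution", at a level set as follows: "the statistical significance level will be (two-sided) 0.05".
- **Group summaries (Statistical analysis).** Mean and standard deviation under normality; otherwise "median [interquartile range] if the distribution is not normal for quantitative parameters".
- **Effect estimate for secondary endpoints (Statistical analysis).** "For quantitative variables the mean difference and its 95% confidence interval will be presented". No normality condition is attached.
- **Costs as an outcome (Outcomes).** One secondary outcome is "to compare in both groups of women the direct and indirect costs of care and the out-of-pocket costs".
- **Economic question (Economic analysis).** "The economic analysis will describe and compare the costs between the two groups of patients", and the first question put is "is the precariousness in breast cancer induces over-costs from the society perspective". The section names the cost components, the perspectives and the human capital approach, but no statistical test.

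**The concern.** A cost to society is a total over patients, so the contrast that answers the economic question is the difference in arithmetic mean cost. Per-patient costs are usually right-skewed, and out-of-pocket costs often contain many zeros. Under the printed rule such data go to Wilcoxon and the median. Wilcoxon asks whether a randomly chosen precarious patient tends to cost more than a randomly chosen non-precarious one. That is not a comparison of means, and a minority of very expensive pathways moves it little.

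The report would then carry a mean difference with its interval beside a p-value and group summaries that concern something else. If they disagree, the text gives no rule for which settles the question, and the significance level attaches to the test. At stake is the conclusion on one named secondary objective: a real excess in mean cost could be reported as non-significant, or appear beside a significant result in the opposite direction.

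**Working it through.** **Step 1. Does the rule reach costs?** Costs are a compared secondary outcome (Outcomes). Economic analysis names no test of its own, and the rule in Statistical analysis covers quantitative variables without exception. As printed, it applies to costs.

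**Step 2. The document's own figure.** No cost mean, standard deviation or power is stated. The only figure to reproduce is the sample size for stage (50% against 60%, 90% power, two-sided 0.05):

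n = [1.960 × √(2 × 0.55 × 0.45) + 1.282 × √(0.5 × 0.5 + 0.6 × 0.4)]² / 0.10² ≈ 518.0, rounded up to 519 per group, against 520 stated. It agrees. Costs play no part in it, so it is used below only as the group size.

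**Step 3. Lognormal illustration (all cost inputs assumed).** For median m and log-standard deviation s:

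- mean = m × exp(s²/2)
- P(A > B) = Φ[(ln m_A − ln m_B) / √(s_A² + s_B²)], the quantity Wilcoxon responds to (A = precarious, B = non-precarious)

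Scenario (a) worked through: mean A = 9,000 × exp(0.5) = 14,838; mean B = 10,000 × exp(0.245) = 12,776; difference +2,062. P(A > B) = Φ(−0.1054 / 1.2207) = 0.466, below one half. Mean and rank comparison point in opposite directions.

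Simulation: 520 per group, 2,000 replicates, Wilcoxon rank-sum and Welch t test, two-sided 0.05.

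| | A: m, s | B: m, s | Mean difference | P(A > B) | Wilcoxon significant: A lower / A higher | Welch significant: A lower / A higher |
|---|---|---|---|---|---|---|
| (a) | 9,000, 1.0 | 10,000, 0.7 | +2,062 | 0.466 | 49% / 0% | 0% / 56% |
| (b) | 8,500, 1.0 | 10,000, 0.6 | +2,042 | 0.445 | 86% / 0% | 0% / 67% |
| (c) | 10,000, 1.0 | 10,000, 0.7 | +3,711 | 0.500 | 2.5% / 3.1% | 0% / 97% |
| (d) | 11,000, 0.8 | 10,000, 0.8 | +1,377 | 0.534 | 0% / 45% | 0% / 35% |
| (e) | 9,000, 0.7 | 10,000, 0.7 | −1,278 | 0.458 | 67% / 0% | 56% / 0% |

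In (a) and (b) Wilcoxon contradicts the mean. In (c) it misses a difference that Welch nearly always finds. In (d) and (e), with equal log-spread, the two agree in direction and Wilcoxon has somewhat more power. The 95% interval for the mean difference covered the true value in 94% to 96% of replicates throughout.

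**Step 4. A costly minority (also assumed).** Gamma base cost with mean 15,000 euros in both groups, plus about 40,000 euros in 16% of precarious and 10% of non-precarious patients. Mean difference = (0.16 − 0.10) × 40,000 = +2,400 euros. Over gamma shapes 1 to 4 and several forms of the tail, power was about 36% to 72% for the mean comparison and about 25% to 40% for Wilcoxon.

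If the precarious base mean is instead 13,800, the mean difference is 2,400 − 1,200 = +1,200 euros. The median difference then ran from about +315 to about −600 depending on shape. Wilcoxon was significant in the wrong direction in only about 0.5% to 11% of replicates, and the mean comparison was significant in about 12% to 27%. Most such trials would give two non-significant results.

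**The case against.** The strongest reply is that the relevant estimate is already planned. The sentence on secondary endpoints commits to a mean difference with a 95% interval, whatever the distribution, and is more specific than the general paragraph on tests. A reader might infer from the Wilcoxon rule that the plan leaves the societal cost question unanswered; the text does not support that. The mean difference answers it, and its interval performed well in every lognormal scenario above. This stands, and it limits the point to a mismatch between the test and summaries on one side and the estimate on the other.

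A reader might also infer that a reversed result is to be expected. That is not supported either. The article gives no cost mean, spread, tail or proportion of zeros. Reversal was frequent only under clearly unequal lognormal spread, rare in the costly-minority scenario, and absent with equal log-spread.

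Finally, bootstrap details, two-part models and covariate adjustment are commonly left to a full protocol or analysis plan, neither of which is shown, so their absence is no fault. That also stands. It does not remove the mismatch, because the article does state a test rule, and as printed that rule extends to costs.

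**Conclusion.** The point holds in a limited form. The mean cost difference and its interval are planned and address the economic question. For skewed costs, the p-value and group summaries in the same section would refer to another quantity, and nothing says which governs the conclusion. They can miss a real difference in mean cost, as in (c), where Wilcoxon was significant in about 6% of replicates against 97% for Welch. If spread or shape differs between groups they can also point the other way.

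Two assumptions carry this: that costs will be skewed enough to trigger the switch, which is usual but not stated, and that the groups differ in spread or shape, which the article does not quantify. All cost figures here are illustrations and not forecasts. Severity is minor: one secondary objective is affected, while the primary endpoint, sample size and data collection are not.

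**What to change.** Add a sentence to Statistical analysis, or to Economic analysis, that exempts cost outcomes from the normality-based switch. For each cost outcome:

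- report the arithmetic mean by group;
- base both the test and the 95% confidence interval on the mean difference, for example by Welch, by bootstrap, or by a generalised linear model that reports marginal mean differences;
- give the median and interquartile range as description only, without a Wilcoxon p-value.

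The choice among these methods is secondary; what matters is fixing, before cost data are analysed, that the mean difference decides. If a fuller analysis plan already treats costs separately, a cross-reference is enough.

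The cost is wording only. Means are sensitive to a few extreme values, and where groups differ by a common scale factor the mean comparison has somewhat less power than Wilcoxon (35% against 45% in scenario d). That is an acceptable price for a test that addresses the question asked.

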Third, variations in access and quality of care for people with breast cancer could also explain differences in survival rates. The French health insurance system ensures patient access to the most effective treatments, regardless of income level and type of insurance [12]. This provides rather good healthcare access compared to other western countries, but also hide greater inequalities [4]. It has also been shown an association between socioeconomic status and quality of oncology care, with, for example, fewer participation of low-income patients in clinical trials suggesting unequal access to the newest cancer treatments [13]. The remoteness of specialized centers and living in an area with significant economic and social precariousness can reduce significantly the likelihood of patients to access to the best quality of care. From an economic point of view, precariousness increases both hospital length of stay and cost [14]. Thus, in breast cancer, Medicaid patients who underwent surgical resection (+ − reconstruction) had a higher length of stay than private insured patients [15].

The description and analysis of the care pathway has been the subject of numerous works including sociological and anthropological studies, which invariably note its diversity, plurality and complexity. This complexity is part of our multicultural contemporary societies [16]. The context of free movement of ideas, people and products causes a multiplication of health actors from various backgrounds. Anthropological studies about care pathway in precarious situations are less common [17, 18]. Moreover, most of epidemiologic and health economics studies are focused on the economic determinants possibly linked to the different forms of social protection. However, as we mentioned earlier, precariousness is not only connected to the material conditions of existence. Precariousness also refers to relationships that patients have with their lifetime, with others, with their own body, relationships that determine their behaviors. In addition, the social and health environment can facilitate or hinder the access to specialized services and professionals. Reasons of renunciation or delay in screening and care have to be described in the specific setting of the course of breast cancerand of breast cancer treatment [17].

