## Methods and design

### Study design and outcomes

#### Study design

The DESSEIN (“**D**isparités **E**conomiques et **S**ociales et cancer du **SEIN”**) is an academic, investigator-driven, prospective observational multicenter cohort study comparing patients “Exposed” to precariousness to patients “unexposed” to precariousness.

Three scores of precariousness will be applied to patients for determining precariousness:
EPICES score [21]Pascal score [22]The most relevant basic needs retained in the study of the French version of EDI (European Deprivation Index) [23].

Precariousness will be defined by identification of this condition by at least one of the three scores. Absence of precariousness is defined by absence of identification of this condition by the 3 scores.

Each precarious patient will be matched to a non- precarious patient belonging to the same age group, regardless of the center. Each woman will receive breast cancer treatment according to stage of the disease and to local multidisciplinary procedures of each center. In France, treatment decisions are made during multidisciplinary meetings in agreement with the national and international recommendations and/or with the local referential.

Deprived patients are compared to non-deprived patients in the breast cancer care pathway.

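### Crude two-group comparison of treatments received cannot separate a care gap at equal stage from the consequence of later stage; an equal-stage estimate should be added

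*Protocol article*

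**What the plan says.** All references are to the protocol article.

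- **Statistical analysis.** Groups are compared by t or Wilcoxon tests and by chi-square or Fisher tests. The primary endpoint gets a two-sided chi-square test and an odds ratio. Then: "For secondary endpoints, the same principle will be applied for qualitative variables". The next sentence gives quantitative variables a mean difference with a 95% confidence interval. No stratification, model or adjustment for stage is named.
- **Study design.** Each precarious patient is matched to a non-precarious one "belonging to the same age group, regardless of the center", so stage is not balanced by design. The same section states that a woman's treatment depends on her stage and on her centre's procedures.
- **Determination of sample size.** "Our hypothesis is that the proportion of stage 1 patients will be 50% among precarious patients versus 60% among non-precarious".
- **Outcomes.** One secondary outcome is "to compare those pathways between precarious and non-precarious women"; another compares direct, indirect and out-of-pocket costs.
- **Background.** After late screening and delay to treatment, a third possible mechanism is raised: "variations in access and quality of care for people with breast cancer could also explain differences in survival rates".
- **Data management.** Stage, treatments received and the delay from diagnosis to first treatment are all taken from the medical record.

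**The concern.** Three statements meet here: stage is expected to differ between the groups, treatment follows stage, and treatments are compared without regard to stage. If the primary hypothesis is true, any treatment whose use varies with stage will differ between the groups even when women at the same stage are treated identically. The crude odds ratio then combines two things: the downstream effect of later diagnosis, and any difference in care between women at the same stage. The Background treats these as distinct mechanisms, and Expected results and perspectives lists measures that address one or the other. The mixture can also run the other way, with less treatment at a given stage offset by more advanced stage, so that a real gap goes unseen.

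**Working it through.** **Inputs from the document.** Stage 1 in 50% (precarious) and 60% (non-precarious); 520 per group; "the statistical significance level will be (two-sided) 0.05"; "To detect such a difference with a 90% power, 520 patients are needed".

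**The plan's own figure.** With pooled variance and no continuity correction,

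n = [1.960·√(2·0.55·0.45) + 1.282·√(0.50·0.50 + 0.60·0.40)]² / 0.10² ≈ 518.04, rounded up to 519 per group.

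Power at 520 is 90.1%. The stated 520 is reproduced; the sample size is not at issue.

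**Crude difference with identical care within stage.** Let a be the treatment rate in stage 1 and b the rate beyond, the same in both groups. Then

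- precarious: p₁ = 0.5a + 0.5b
- non-precarious: p₂ = 0.6a + 0.4b
- difference: p₁ − p₂ = 0.1(b − a)

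The probability that the crude test reaches p<0.05 is Φ[(d − 1.96·s₀)/s₁] + Φ[(−d − 1.96·s₀)/s₁]. Here d = p₁ − p₂, s₀ = √(2p̄(1−p̄)/520) with p̄ the mean of p₁ and p₂, and s₁ = √{[p₁(1−p₁) + p₂(1−p₂)]/520}.

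The documents give no values for a and b, so these pairs are assumptions:

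| a, stage 1 | b, beyond | p₁ | p₂ | Crude odds ratio | Crude p<0.05 |
|---|---|---|---|---|---|
| 20% | 40% | 30% | 28% | 1.10 | 11% |
| 20% | 50% | 35% | 32% | 1.14 | 18% |
| 30% | 70% | 50% | 46% | 1.17 | 25% |
| 20% | 70% | 45% | 40% | 1.23 | 37% |
| 20% | 80% | 50% | 44% | 1.27 | 49% |

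Worked line for 20% and 80%: d = 0.06, s₀ = 0.03095, s₁ = 0.03090; (0.06 − 1.96·0.03095)/0.03090 ≈ −0.02; Φ ≈ 0.49.

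The result is driven by the gap b − a, here 20 to 60 points. A smaller gap gives less: 30% and 40% gives d = 0.01 and about 6%.

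**Check by simulation** (20,000 runs per pair). The crude chi-square rejected in 11% (20/40), 17% (20/50), 26% (30/70) and 49% (20/80) of runs. A stage-stratified Cochran-Mantel-Haenszel test rejected in 5.0% in all four.

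**Masking.** Assume 30% treated in stage 1 in both groups, but beyond stage 1 80% of non-precarious and 70% of precarious women.

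- non-precarious: 0.6·30 + 0.4·80 = 50%
- precarious: 0.5·30 + 0.5·70 = 50%

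The crude difference is zero. Beyond stage 1 there would be 0.4·520 = 208 and 0.5·520 = 260 women. The standard error is √(0.8·0.2/208 + 0.7·0.3/260) = 0.040, so the 10-point gap is about 2.5 standard errors and visible once stage is separated.

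**Quantitative outcomes.** If an outcome differs by stage by 0.5, 1 or 2 within-stage standard deviations (assumption), the crude mean difference is 0.05, 0.10 or 0.20 standard deviations. It is significant in 12%, 30% or 63% of studies.

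**The case against.** **The crude contrast is not wrong in itself.** Stage lies on the path from precariousness to treatment and cost, so it is a mediator and not a confounder. The stated aim is the impact of precariousness on pathways and treatment, and the crude contrast estimates that total effect. This stands. The percentages above are not false-positive rates for the total difference, which is real in those scenarios. They are misleading only if read as evidence of unequal care.

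**Costs.** A reader might infer that the cost comparison is equally flawed. The Economic analysis section asks whether precariousness induces extra cost to society. Cost caused by later diagnosis belongs in that answer, and holding stage equal would remove it.

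**Delays.** A reader might extend the point to the delay from diagnosis to first treatment. The document does not tie that delay to stage; the Background attributes it to diagnostic context, local resources and individual factors.

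**Interpretation.** No passage says that crude differences will be attributed to quality of care. Access and quality appear as a background mechanism for survival differences, not as a listed objective. That the results will be misread is therefore a risk, not something the plan announces.

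**Condensed article.** A fuller protocol or analysis plan may contain stage-stratified analyses, and their absence here would not by itself be a finding. The sections on geographical and anthropological analysis and on expected results do speak of relating precariousness to clinico-pathological data. But neither names a comparison at equal stage, and the article does state a method for secondary endpoints. That method is what is assessed here.

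**Conclusion.** The point holds for treatments received. The stated comparison gives a valid total difference but cannot attribute it to access or quality of care, because the study's own hypothesis and its own account of treatment imply a stage-driven difference. For the assumed pairs of stage-specific rates, the crude test is significant in about 11–49% of studies with identical care within stage, and a 10-point gap beyond stage 1 can cancel exactly. These sizes rest on assumed rates, on stage reduced to stage 1 versus beyond, and on the hypothesised 50% versus 60%.

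The stronger conclusion, that all secondary comparisons are invalid or that delays and societal costs will be misjudged, is not supported. The primary analysis and the sample size are unaffected. This is a worthwhile addition to the secondary analysis, not a replacement of it.

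**What to change.** 1. Keep the total difference between groups, crude or age-adjusted, for all secondary endpoints. It remains the main answer to the societal cost question.
2. For treatments received, pre-specify a second comparison at equal stage: stage-stratified, or a regression on group, stage category and age. Show the stage-specific estimates as well as the pooled one, since a gap confined to later stages is diluted by pooling.
3. As a supplement, do the same for direct medical costs and for other pathway outcomes that prove to depend on stage.
4. Base statements about access to or quality of care on the equal-stage estimate. State its limit: stage is a mediator, and common causes of stage and treatment, such as tumour biology, may remain after adjustment for stage and age.

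The cost is a few extra analyses on data already collected and somewhat lower precision at equal stage. No extra patients, visits or questionnaires are needed.
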